### Type of analysis

#### Data entry and security

The household responses to the questionnaires will be entered twice by independent operators who are ignorant of intervention status of the sites, with verification of discordant entries from the original questionnaires. A data manager ignorant of intervention status of the sites will check digitised data for logical errors. Questionnaires from intervention and control sites will be handled in exactly the same way, with all data technicians unaware of the intervention status of clusters. Site identities will be masked before analysis.

#### Principal analysis

With 150 clusters allocated evenly between intervention and control arms, the cluster analysis of primary outcomes will rest on a t-test, following an intention-to-treat principle (everyone included in each cluster, per allocation). The simultaneous evaluation in control and intervention sites will account for temporal effects. Serological status, reports of dengue illness, and vector indices lend themselves to analysis as continuous variables. Recent infection in children, adopting a cut-off of a two-fold increase of IgG units between samples, and pupae-positive households, are both dichotomized variables; the percent of households with serological evidence of recent infection in any child or with larvae/pupae-positive entomology serves as a continuous variable in each site. We will report outcomes as absolute event rates among intervention and control groups, with relative risk reduction (RRR) and 95% confidence intervals.

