**Methods/Design:**

The Camino Verde (Green Way) is a pragmatic parallel group trial of pesticide-free dengue vector control, adding effectiveness to the standard government dengue control. A random sample from the most recent census in three coastal regions of Guerrero state in Mexico will generate 90 study clusters and the equivalent sampling frame in Managua, Nicaragua will generate 60 clusters, making a total of 150 clusters each of 137–140 households. After a baseline study, computer-driven randomisation will allocate to intervention one half of the sites, stratified by country, evidence of recent dengue virus infection in children aged 3–9 years and, in Nicaragua, level of community organisation. Following a common evidence-based education protocol, each cluster will develop and implement its own collective interventions including house-to-house visits, school-based programmes and inter-community visits. After 18 months, a follow-up study will compare dengue history, serological evidence of recent dengue virus infection (via measurement of anti-dengue virus antibodies in saliva samples) and entomological indices between intervention and control sites.

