## Methods/Design

### Design of the study

This parallel group pragmatic cluster randomised controlled trial will test informed community mobilisation in dengue control, measured by risk of dengue virus infection, occurrence of self-reported dengue cases, and vector density. The baseline will include a household questionnaire, entomological assessment and saliva samples from children aged 3–9 years. After the baseline survey, a sampling statistician not associated with the trial will randomise the 150 sites to intervention or control, stratified by area, entomological indices and serological evidence of recent dengue virus infection in children. Interventions will be based on evidence of *Aedes aegypti* infestation, explanation of the dengue vector life cycle, and information on how to prevent larvae and pupae from becoming adult mosquitoes. Different ways of transmitting this knowledge and acting upon it will be designed and implemented by the participating communities. The intervention will run for at least a full year. A multi-method impact survey will cover all 150 clusters with no in-cluster sampling. This will measure risk of dengue virus infection, disease reports, and entomological indices of the vector *Aedes aegypti*. Figure 1 is a flow-diagram of the trial.

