### Power calculation

Data from the feasibility study in Managua facilitated sample size estimation. Using the dengue serology results as the principal outcome, control communities in 2004–8 showed a range of 1.5% to 7.4% (k-statistic 0.328). Follow-up of 40 children in each of 150 clusters (75 clusters per arm) would detect a 33.3% reduction in incidence (4.5% to 3%) with 80% power at a significance level of 5%. These calculations assume no interaction effects and a two-sided test with cluster as unit of primary analysis in unmatched parallel groups. Calculations used a spreadsheet based on the trial simulator devised by Taylor and colleagues [35].

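### The principal t-test carries no term for the randomisation strata, so it is valid but conservative to the extent that the strata predict outcome, and two sections list different strata

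*Protocol article*

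**What the plan says.** The Principal analysis section states that "the cluster analysis of primary outcomes will rest on a t-test, following an intention-to-treat principle". It adds that each site's percentage serves as a continuous variable and that relative risk reductions with 95% confidence intervals will be reported. It names neither strata nor baseline values. The Secondary analysis section plans individual-level models that account for temephos exposure and water supply; it names no strata either.

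The Allocation concealment section says that allocation is by random numbers within strata defined by the baseline study. The strata themselves are described twice:
- Abstract, Methods/Design: "stratified by country, evidence of recent dengue virus infection in children aged 3–9 years and, in Nicaragua, level of community organisation".
- Design of the study: "stratified by area, entomological indices and serological evidence of recent dengue virus infection in children".

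The Power calculation section assumes "a two-sided test with cluster as unit of primary analysis in unmatched parallel groups". It gives "Follow-up of 40 children in each of 150 clusters (75 clusters per arm"), which "would detect a 33.3% reduction in incidence (4.5% to 3%) with 80% power at a significance level of 5"%, using Managua data in which "control communities in 2004–8 showed a range of 1.5% to 7.4% (k-statistic 0.328").

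**The concern.** Randomising within strata balances the arms on whatever the strata capture, so that variation drops out of the treatment difference. A two-sample t-test on all 150 cluster values still counts it as error. The estimated standard error is then larger than the true one, the interval over-covers and the test runs below 5%.

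Country is the obvious case: 90 clusters are in Guerrero and 60 in Managua. The planning k comes from Managua control communities alone, so it holds no between-country variation, whereas the pooled t-test would meet that variation.

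The two lists of strata matter because an analysis that respects the design needs to know the design. Child serology is in both. Community organisation is only in the Abstract, and entomological indices are only in the Design of the study section. One gives country, the other area. The Allocation concealment section names no factor, so it does not settle the conflict.

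**Working it through.** **1. The plan's own figure.** Inputs from the Power calculation section: p0 = 0.045, p1 = 0.03, m = 40, c = 75 per arm, k = 0.328, two-sided 5%. The unmatched cluster formula is

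c = 1 + (1.96 + 0.8416)² × [p0(1−p0)/m + p1(1−p1)/m + k²(p0² + p1²)] / (p0 − p1)².

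- Binomial part: (0.042975 + 0.0291)/40 = 0.001802.
- Between-cluster part: 0.1076 × 0.002925 = 0.000315.
- Sum: 0.002117, so c = 1 + 7.849 × 0.002117/0.000225 = 74.8.

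The plan's 75 clusters reproduce, with power 80.1% (t distribution, 148 df).

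**2. If total k, both countries together, is 0.328.** Between-cluster variation is 0.000315/0.002117 = 15% of the variance of a cluster proportion. Even strata that explained all of it would raise power only from 80.6% to 86.4% (normal approximation) and shorten the half-width of the interval from 1.04 to 0.96 percentage points.

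**3. If country adds variation on top of k = 0.328.** Assume incidence pM in Mexico (share 0.6) and pN in Nicaragua (share 0.4), with the mean kept at 4.5% and risk ratio 2/3. Summing over arms:
- V_W = weighted mean of p(1−p)/40 + k²p² within country;
- V_B = 0.6 × 0.4 × (pM − pN)².

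The true SE is √(V_W/75). The t-test uses √((V_W + V_B)/75). With d = 0.015, t-test power ≈ Φ[(d − 1.976 × SE of the t-test)/true SE]; for the adjusted test the true SE stands in both places.

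| Assumed pM / pN | V_W | V_B | SE ratio | t-test | Adjusted |
|---|---|---|---|---|---|
| 4.5% / 4.5% | 0.002117 | 0 | 1.00 | 80% | 80% |
| 5.5% / 3.0% | 0.002134 | 0.000217 | 1.05 | 77% | 80% |
| 6.5% / 1.5% | 0.002188 | 0.000867 | 1.18 | 67% | 79% |

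Third row in full: V_B = 0.24 × (0.05² + 0.0333²) = 0.000867; true SE = 0.00540; t-test SE = 0.00638. Power is Φ[(0.015 − 0.01261)/0.00540] = Φ(0.44) = 67%, against Φ(2.78 − 1.976) = 79%.

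Simulation with 90 + 60 clusters randomised within country agrees: no loss with equal incidence, 78–79% vs 81% in the second row, and 67–69% vs 79–80% in the third. The t-test's type I error is then about 5%, 3.7% and 1.6% respectively.

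**4. House Index, assumed 20% in Mexico and 45% in Nicaragua, 140 houses per cluster.** Per arm under no effect, V_B = 0.24 × 0.25² = 0.0150.
- With the protocol's ICC of 0.396 (Intraclass correlation coefficient section), the variance of a cluster value is p(1−p)(0.396 + 0.604/140): 0.0641 in Mexico and 0.0991 in Nicaragua, weighted 0.0781. SE ratio = √(1 + 0.0150/0.0781) = 1.09 (1.08 under a 15% relative reduction). Power for that reduction is about 13–14% vs 17–18%.
- With an assumed k of 0.3, the variance is k²p² + p(1−p)/140: 0.00474 and 0.01999, weighted 0.0108. SE ratio = √(1 + 0.0150/0.0108) = 1.54 (about 1.55 in simulation). Power is about 42% vs 80–81%.

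The documents do not decide between these. At the mean level of 30%, an ICC of 0.396 corresponds to k = √(0.396 × 0.7/0.3) = 0.96. The feasibility range of 11% to 50% of households positive, taken as four standard deviations, suggests (0.39/4)/0.305 = 0.32.

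**The case against.** The strongest reply is that nothing is broken. The trial was sized for a cluster-level two-sided comparison, the analysis uses that unit, and the stated power reproduces. There is no bias and no inflated type I error, so a positive result stands. All of this is right.

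Several stronger readings are tempting but not supported:
- A reader might infer that the trial is underpowered or the test invalid. The loss depends on how far the strata predict outcome, which the documents do not say; with equal country levels it is nil.
- A reader might take the House Index result at k = 0.3 as the expected loss. It is one end of a range whose other end uses the protocol's own ICC.
- A reader might assume that every outcome has a baseline value of the same kind. The serological outcome is a two-fold rise across paired samples around the 2012 season, and the baseline is said only to include saliva samples. A like-for-like baseline for serology is not established.
- A reader might take unmatched to mean unstratified. It need mean only that clusters were not paired.

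It can also be said that a stratified cluster-level t-test is still a t-test, and that stratum terms may sit in a fuller plan not shown here. That is fair, and it keeps the point a recommendation. It does not remove the conflict between the two lists of strata, which is in the published text.

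**Conclusion.** The point holds as a matter of efficiency. The named t-test is valid and conservative under stratified allocation, and it delivers the planned 80% power under the planning assumptions. Including the strata would give narrower intervals and more power wherever the strata are prognostic, and would cost almost nothing where they are not.

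For serology the plausible gain runs from zero to about 11 points (12 by the formula), the upper figure needing a more than fourfold difference in incidence between countries. For the House Index it may be slight or large, depending on a between-cluster variance that the documents leave open. Every country contrast used here is an assumption.

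The disagreement over the strata is a separate, plain inconsistency. It does not affect an unadjusted t-test, but it must be corrected before any stratified analysis can be specified.

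**What to change.** 1. State one and the same set of strata in the Abstract and in the Design of the study section, as actually used for allocation.
2. Make the principal analysis a cluster-level regression of the site value on arm with those strata as fixed effects, at minimum country; a stratified t-test would also serve. Add the cluster's baseline value where the same or a comparable measure exists, for example entomological indices and reported dengue.
3. A linear model of percentages gives an absolute difference, not the promised relative risk reduction. Specify that the reduction and its 95% interval come from the same adjusted analysis: a ratio of adjusted means with a delta-method or bootstrap interval, or a model on the log scale.
4. Keep the plain t-test as a sensitivity analysis, and settle the choice before site identities are unmasked.

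The cost is a few of 148 degrees of freedom, plus specifying the relative measure. No new data are needed.

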### Outcomes

The main outcome measures are (i) risk of dengue virus infection as measured by a minimum of two-fold increase in anti-dengue virus IgG antibodies across paired saliva samples collected before and after the 2012 dengue season in children aged 3–9 years [20] (ii) dengue cases (any age) in the last year reported by the household respondent; and (iii) entomological indices of *Aedes aegypti* breeding sites, using the protocol developed in the Nicaragua feasibility study [21].

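### The principal analysis summarises serology per household, with no stated denominator, while the outcome, planning rates and sample size are per child

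*Protocol article*

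**What the plan says.** The Outcomes section defines serological outcome (i) in individual children: "a minimum of two-fold increase in anti-dengue virus IgG antibodies across paired saliva samples collected before and after the 2012 dengue season", in those aged 3–9 years. The feasibility section on the standard deviation of the outcome measure gives 1.5% to 7.4% as incidence in children in the control communities. The Power calculation takes up that range, with k = 0.328. It counts 40 children in each of 75 clusters per arm to detect a fall from 4.5% to 3% with 80% power, two-sided at 5%.

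In the Principal analysis, "the cluster analysis of primary outcomes will rest on a t-test". The dichotomy starts at child level: "Recent infection in children, adopting a cut-off of a two-fold increase of IgG units between samples, and pupae-positive households, are both dichotomized variables". The only serological summary then given for a site is "the percent of households with serological evidence of recent infection in any child". The reporting sentence names no unit: "We will report outcomes as absolute event rates among intervention and control groups, with relative risk reduction (RRR) and 95% confidence intervals".

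The Secondary analysis returns to individual children, in a mixed model.

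**The concern.** A cluster-level t-test compares whatever single number is computed for each cluster. As the text stands, that number for serology is a household percentage, which is not the defined outcome and not the quantity that was powered. A household percentage depends on how many households contain a sampled child and how many children are sampled in each, as well as on the children's risk.

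Two things are at stake. First, the article promises absolute event rates, and its Economic analysis section names the serological end-point as the most relevant for direct impact and speaks of costing cases avoided. Both need a rate with a known unit. Second, if the denominator is all households, a household without a paired sample has no serological result but would still count as uninfected. Until one definition is fixed, a child rate, a rate among households with a sampled child and a rate among all households all remain open to the analyst.

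**Working it through.** **Inputs.** From the Power calculation: p0 = 0.045, p1 = 0.03, m = 40 children per cluster, 75 clusters per arm, k = 0.328, two-sided 5%, power 80%. From Serology samples: about 140 households per cluster and one child aged 3–9 in every three households. From The setting: 100–120 households per cluster. From Adherence/compliance rates in the feasibility study: 2,992 samples from 3,217 households with children.

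**Step 1: reproduce the plan's figure per child.** The usual formula for unmatched clusters is

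c = 1 + (z₀.₉₇₅ + z₀.₈₀)² × [p0(1−p0)/m + p1(1−p1)/m + k²(p0² + p1²)] / (p0 − p1)².

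- p0(1−p0)/m = 0.045 × 0.955/40 = 0.001074
- p1(1−p1)/m = 0.03 × 0.97/40 = 0.000728
- k²(p0² + p1²) = 0.1076 × 0.002925 = 0.000315
- Sum = 0.002117. Divided by 0.015² = 0.000225, this gives 9.407.
- c = 1 + 7.849 × 9.407 = 74.8, rounded up to 75. Power at 75 clusters is 80.1%.

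The stated sample size is therefore correct, and it is counted in children.

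**Step 2: the same child risk as a household percentage.** The article gives neither the denominator nor the number of sampled children per household, so these are assumed ranges with k held at 0.328 and 40 children per cluster.

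- All H households counted, one sampled child per household: rate = 40p/H. With H = 140, 1.8/140 = 1.29% against 1.2/140 = 0.86%.
- Only households with a sampled child, averaging 1 + q children as a mix of one-child and two-child households, with independent infections: rate = (1−q)p + q[1 − (1−p)²]. With q = 0.5, 0.5 × 4.5% + 0.5 × 8.80% = 6.65% against 0.5 × 3.0% + 0.5 × 5.91% = 4.46%.

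| Cluster summary | Units per cluster | Control vs intervention | RRR | Power, 75 per arm |
|---|---|---|---|---|
| Children with paired samples | 40 | 4.50% vs 3.00% | 33.3% | 80.1% |
| All households, H = 140 | 140 | 1.29% vs 0.86% | 33.3% | 79.1% |
| All households, H = 100 | 100 | 1.80% vs 1.20% | 33.3% | 79.3% |
| Households with a sampled child, 1.25 each | 32 | 5.57% vs 3.73% | 33.1% | 79.6% |
| Households with a sampled child, 1.5 each | 26.7 | 6.65% vs 4.46% | 33.0% | 79.3% |

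The control rate spans a factor of about five (6.65/1.29 = 5.2) for one and the same child risk. The absolute reduction is 1.5 points per child, about 0.43 points over all 140 households, and about 2.2 points in the last row. The relative reduction and the power barely move.

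**Step 3: sibling dependence.** If infections in siblings are partly dependent (midway between independent and complete), power in the last two rows falls to about 76% and 73%. This rests on an assumption, and such dependence would also reduce the precision of a per-child analysis. It cannot be charged to the household summary alone.

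**Step 4: loss of pairs under the all-household denominator.** As an illustration, take no true effect, a child risk of 4.5% in both arms, 40 paired children per control cluster and 36 (10% fewer) per intervention cluster, with 140 households in each. The rates are 0.045 × 40/140 = 1.29% and 0.045 × 36/140 = 1.16%, an apparent RRR of 1 − 36/40 = 10%. Per paired child both arms show 4.5%, and this arithmetical artefact disappears.

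**The case against.** The strongest reply is that little of inferential weight changes. Dividing the same infections by about 140 households instead of 40 children is mostly a change of scale, to which a t-test is indifferent. The relative reduction and the 75 clusters per arm survive almost intact. That stands.

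The all-household denominator is also only one reading, and arguably the less natural one, since a household with no sampled child has no serological result. The feasibility figures point the same way: 2,992/3,217 = 0.93 samples per household with children, with the shortfall of 225 put down to refusal or absence. If only households with a sampled child are counted, household and child rates could nearly coincide. That also stands as a likelihood. But the article does not state that denominator, and the wording about any child allows for more than one per household.

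Randomisation balances household composition in expectation, so composition alone does not bias the comparison. Loss of paired samples, however, arises after allocation. The Missing data section itself treats self-selection as a concern because of the engagement that the intervention involves. It plans multiple imputation for the serological outcome, which could limit the effect in Step 4, but it does not name the unit that is imputed.

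Finally, the reporting sentence names no unit, and a child-level model is planned. It is therefore an inference, not a stated fact, that the headline rate will be per household. The child-level model is secondary, so it does not settle what the principal test compares.

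**Conclusion.** The mismatch is real and lies in the current text. The serological outcome, its planning rates and its sample size are per child, while the only site-level serology summary given for the principal t-test is per household, with an open denominator. It calls for a moderate correction.

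The size is as follows. The absolute control rate could lie anywhere from about 1.3% to about 6.7% for a child risk of 4.5%, under the assumptions shown. The RRR stays at about 33%, and power at about 79–80% when infections within households are independent. Differential loss of pairs could distort the RRR, but only if all households are counted and missing pairs are not imputed; the 10% figure is an illustration, not a forecast.

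A reader might infer three stronger things, and the documents support none of them. The trial is not shown to be undersized: its figure reproduces. A threefold loss of effect does not follow from the all-household reading, because both arms shrink together. A doubling of rates from two-child households is not to be expected either, because nothing in the article makes two sampled children typical.

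**What to change.** In the Principal analysis, define the serology summary for each cluster as the number of children with a two-fold or greater IgG rise divided by the number of children with paired pre- and post-season samples in that cluster. State that the absolute event rates and the RRR for this outcome are per child.

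Use the household percentage for entomology, where it matches the House Index. A household serology percentage may stay as a supplementary summary if its denominator is stated as households with a sampled child.

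The cost is about one sentence. No extra data are needed and the sample size does not change. The definition should be settled before unblinded analysis.

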#### Secondary analysis

We will use individual-level data allowing for informative clustering in a non-linear mixed model with a robust variance and non-fixed odds-ratio [27] or generalised linear mixed model (GLMM) assuming cluster as a random effect [28]. We propose to examine average individual effects (for example, children with increased serological evidence of recent dengue virus infection, recent self-reported cases of dengue, or entomological parameters) while accounting for temephos exposure and water supply.

Sensitivity analysis will focus on gender-specific responses and exclusion of sites with prominent government pesticide intervention.

Planned subgroup analysis will focus on regional variations of the protective effect of Camino Verde, especially relating to population density (urban/rural) and the particular choices of intervention.

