### Objectives of the Camino Verde trial

The research question is: Among residents of Managua and the State of Guerrero in Mexico, does evidence-based community mobilisation add effectiveness to the usual dengue control strategies to decrease the risk of dengue virus infection using a parallel group cluster RCT?

The Camino Verde hypothesis is that informed community mobilisation adds effectiveness in controlling dengue. The trial is concerned with the real-life effect of the intervention in the coastal region of Guerrero state and in Managua, rather than its effectiveness under ideal conditions [15, 16].

The overall objective is to reduce dengue risk through evidence-based knowledge translation. An explicit objective is to develop a sustainable community-oriented vector control approach that reduces the need for pesticides in water used in or around homes or areas that children frequent, or likely to be used with food or even as drinking water.

Specific objectives are (1) Determine entomological and serological status of the virus-vector-host ecosystem as well as knowledge, attitudes and behaviour underlying community-led interventions; (2) In partnership with intervention communities, translate this knowledge on dengue vector behaviour and immunology into household and community action against dengue; (3) Identify the impact of informed community mobilisation on dengue risk and its added effectiveness regarding other infections, social capital and longer term economic welfare.

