#### Entomology indices

These are a) House Index (HI), number of houses with one or more containers positive for immature *Aedes aegypti* divided by the number of houses sampled multiplied by 100; b) Container Index (CI) number of water-holding containers with immature *Aedes aegypti* divided by the number of water-holding containers inspected multiplied by 100; c) Breteau index (BI) number of water-holding containers with immature *Aedes aegypti* per every 100 households inspected; d) pupae per container or household inspected; and e) pupae per person (pu/per) number of pupae collected over the total number of inhabitants of the households inspected.

Secondary outcomes focus on the social capital gained from community engagement and the partial outcomes toward acceptance of the Camino Verde, including knowledge of and attitude to prevention, intention to change prevention behaviour, agency (collective and self-efficacy), discussion/socialisation, and prevention-related action. Additional secondary outcomes include purchase and use of pesticide, and reduced expenditure on health care as a consequence of dengue virus infection.

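### The individual-level secondary model adjusts for temephos exposure without fixing it at baseline, and one planned subgroup (choice of intervention) has no control counterpart

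*Protocol article*

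**What the plan says.** All the analyses at issue are in the Secondary analysis section of the protocol article.

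- **Model.** Individual-level mixed models estimate effects on recent infection in children, reported dengue and entomological measures "while accounting for temephos exposure and water supply". No time of measurement is given for either covariate.
- **Sensitivity analysis.** One of the two named is "exclusion of sites with prominent government pesticide intervention". Neither a time window nor a threshold is given.
- **Subgroups.** Regional variation in the effect is to be examined, "especially relating to population density (urban/rural) and the particular choices of intervention".

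Other sections treat pesticide use as something the trial should change. The Objectives section sets out to "develop a sustainable community-oriented vector control approach that reduces the need for pesticides in water". The paragraph on secondary outcomes, under Entomology indices, reads: "Additional secondary outcomes include purchase and use of pesticide". The abstract calls the study a "pragmatic parallel group trial of pesticide-free dengue vector control, adding effectiveness to the standard government dengue control".

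On who chooses the activities, Design of the study says: "Different ways of transmitting this knowledge and acting upon it will be designed and implemented by the participating communities". This comes after baseline and randomisation.

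The Principal analysis section specifies a cluster-level t-test by intention to treat and names no covariate.

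**The concern.** The research question is whether mobilisation adds to usual control, which is a total effect. Part of the intended change is less pesticide in household water. If temephos exposure is recorded after allocation, it lies on the path from allocation to infection. Holding it constant removes whatever share of the effect, good or bad, runs through changed temephos use. It can also introduce a spurious association, because households that keep using temephos in one arm may differ in unmeasured ways from those that keep using it in the other. Whether protection holds up when pesticide use falls is the policy question raised under Implications for health services and in the Discussion, and a temephos-adjusted estimate hides it.

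The subgroup by choice of intervention has a different problem, which does not depend on timing. A subgroup effect needs the same subgroup in both arms. A control cluster never chose a package, so comparing the clusters that chose one with all controls mixes the effect of that package with the kind of community that chose it.

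**Working it through.** **1. The plan's own figure.** Inputs from Power calculation: 4.5% against 3.0%, 40 children per cluster, k = 0.328, two-sided 5%, 80% power. The usual formula for unmatched clusters is

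c = 1 + (1.96 + 0.842)² × [p0(1−p0)/m + p1(1−p1)/m + k²(p0² + p1²)] / (p0−p1)²

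The bracket is 0.001074 + 0.000728 + 0.000315 = 0.002117. Then c = 1 + 7.849 × 0.002117 / 0.000225 = 74.8, so 75 clusters per arm; power at 75 is 80.1%. The stated design reproduces. It is powered for a total risk ratio of 3.0/4.5 = 0.667 (RRR 33.3%), and nothing below changes that.

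**2. When each variable is fixed.**

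| Variable | Fixed before randomisation? | Can allocation change it? |
|---|---|---|
| Region, urban/rural | Yes | No |
| Water supply | Not stated | Not evident from the text |
| Temephos exposure | Not stated | Yes, by the trial's own objective, if measured at follow-up |
| Government pesticide activity at a site | Not stated | Uncertain |
| Choice of intervention | No | Exists only in the intervention arm |

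**3. If temephos protects (assumed inputs).** Let a and b be the proportions using temephos in control and intervention, r its risk ratio for infection, with no interaction and no shared causes. Then

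adjusted RR = total RR × [1 − a(1−r)] / [1 − b(1−r)]

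With total RR 0.667 and a = 60%:

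| r | b = 40% | b = 30% |
|---|---|---|
| 0.8 | 0.667 × 0.88/0.92 = 0.638 (RRR 36%) | 0.667 × 0.88/0.94 = 0.624 (38%) |
| 0.7 | 0.667 × 0.82/0.88 = 0.621 (38%) | 0.667 × 0.82/0.91 = 0.601 (40%) |
| 0.6 | 0.667 × 0.76/0.84 = 0.603 (40%) | 0.667 × 0.76/0.88 = 0.576 (42%) |

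Here the adjusted estimate is larger than the total effect.

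**4. If temephos does nothing but shares a cause with infection (assumed inputs).** Half of households are higher-risk, with twice the infection risk. Temephos use in controls is 70% in higher-risk and 30% in lower-risk households. In the intervention arm each falls by 20 points, to 50% and 10%. The total RR is 0.667.

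- Users: the higher-risk share is 0.70 in controls and 0.50/0.60 = 0.833 in the intervention arm. Mean relative risks are 1.70 and 1.833, so RR = 0.667 × 1.833/1.70 = 0.719.
- Non-users: the shares are 0.30 and 0.50/1.40 = 0.357. Mean relative risks are 1.30 and 1.357, so RR = 0.667 × 1.357/1.30 = 0.696.

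Within levels of temephos use the RRR is 28% and 30%, smaller than the true 33.3%. A large simulation on these inputs gave 0.661 unadjusted and 0.701 adjusted, in agreement apart from sampling error.

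**5. Both mechanisms together.** With r = 0.7 added to step 4, the simulation gave 0.715 unadjusted and 0.705 adjusted, so the two nearly cancel. With no difference in temephos use between arms, adjusted and unadjusted estimates agreed.

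Every use rate and risk ratio in steps 3 to 5 is an assumption. The documents give none of them.

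**The case against.** The strongest reply has four parts.

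- **The main result is safe.** The principal t-test uses all clusters as allocated, without covariates. The model, exclusion and subgroups only supplement it. This stands, and it limits the weight of the point.
- **Timing is a detail an article may leave to the full protocol or analysis plan.** If temephos exposure and government activity are taken at baseline, those objections fall away. This partly stands: the text is silent and does not say the values are post-randomisation. The silence still matters here because the same article makes pesticide use an outcome and an objective, so either reading is open and only one estimates the total effect. Under Missing data, new arrivals join the study, and they have no household baseline value.
- **Government pesticide is mainly background in both arms.** The setting describes temephos packets as the standard government strategy, and asking whether results hold without heavily treated sites is reasonable. This largely stands. The Contamination section allows that authorities may act on emerging evidence in control clusters, but it does not mention extra pesticide.
- **No effect of temephos may exist to be adjusted away.** The Discussion reports finding no community-based randomised trial that showed protection. That weakens step 3 but not step 4, which needs no temephos effect.

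None of this rescues the subgroup by choice of intervention, although the reply rightly notes that region and urban/rural in the same sentence are sound.

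**Conclusion.** The point holds for the secondary analyses only. As written, the individual-level model may condition on a variable that allocation is meant to change. If it does, the estimate is not the total added effect of mobilisation and may be biased in either direction. The subgroup by choice of intervention cannot give a randomised contrast, whatever the timing of the other variables. This is worth correcting, but the trial's main conclusion does not depend on it.

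A reader might infer more than the documents support:

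- That the adjustment flatters the intervention. It does so in step 3, but step 4 reverses it, and the documents give no size.
- That the protocol specifies follow-up temephos exposure. It gives no time point.
- That the site exclusion is shown to depend on allocation or on local outbreaks. The textual evidence for the first is thin, and the second is plausible but not stated.
- That the ranges of 36% to 42% and 28% to 30% are estimates for this trial. They are illustrations on assumed inputs.

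**What to change.** In the Secondary analysis section:

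1. Adjust the intervention effect only for temephos exposure and water supply measured before randomisation. Where a household has no baseline value, as with new arrivals, use the cluster's baseline value. If the baseline questionnaire does not record temephos, leave it out of the effect model.
2. Keep follow-up pesticide use as an outcome, or put it in a separately labelled mediation analysis with its assumptions stated.
3. Define the government-pesticide exclusion from pre-randomisation information, or label it exploratory and show it beside the result for all 150 clusters.
4. Present the comparison by choice of intervention as descriptive, within the intervention arm. Keep region and urban/rural as subgroups.

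The cost is mainly wording, and the sample size is unchanged. The trial gives up a little adjustment information and a randomised subgroup estimate by intervention type, which the design could not provide anyway. One point needs checking: the feasibility study listed temephos use and water container type among its covariates, but the article does not say that the main baseline questionnaire records them.
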